## **5. Study Design**

A multi-national, multi-centre randomised, open-label, single period, parallel design study of fully closed-loop insulin delivery compared to standard insulin therapy with a sensor over 6 months in adults with T2D.

The study flow chart is outlined in Figure 2.

**Figure 2:** Study flow chart

[figure not shown]

## **6. Study participants**

### **6.1. Study Population**

Adults aged 18 years and over with type 2 diabetes requiring insulin therapy will be recruited.

#### **6.1.1. Inclusion criteria for all countries**

1. Aged 18 years and older
2. Type 2 diabetes diagnosed for at least 12 months
3. Established on an SGLT2 inhibitor and/or GLP-1 receptor agonist for at least 3 months, or have been offered these therapies previously.
4. Treatment with insulin therapy for at least 6 months
5. HbA1c  $\leq$  15% (140 mmol/mol) analysis from local laboratory or equivalent
6. Willing to wear study devices and follow study instructions
7. Capacity to consent to participate in the study

#### **6.1.2. Exclusion criteria for all countries**

1. Type 1 diabetes
2. Current use of insulin pump
3. Current use of any closed-loop system
4. Any physical/psychological disease or medication(s) likely to interfere with the conduct of the study and interpretation of the study results, as judged by study clinician
5. Known or suspected allergy against insulin
6. Pregnancy, planned pregnancy, or breast feeding
7. Severe visual impairment
8. Severe hearing impairment
9. Medically documented allergy towards the adhesive (glue) of plasters
10. Serious skin diseases located at places of the body, which potentially are possible to be used for localisation of the glucose sensor
11. Illicit drugs abuse
12. Prescription drugs abuse
13. Alcohol abuse

Potential participants with diabetes related retinal disease will not be excluded from the trial. An individualised risk approach will be used, and we will consider delaying recruiting people undergoing active treatment of proliferative retinopathy / maculopathy until treatment is complete.

### **6.1.3. Exclusion criteria specific to Switzerland**

1. Lack of safe contraception for female participants of childbearing potential for the entire study duration
2. Incapacity to give informed consent
3. Not literate in German

### **6.1.4. Exclusion criteria specific to France**

1. Lack of safe contraception for female participants of childbearing potential for the entire study duration
2. Incapacity to give informed consent
3. Not literate in French
4. Patient participating in another research protocol including an exclusion period still in progress
5. Patient under the protection of justice or guardianship

### **6.1.5. Exclusion criteria specific to Germany**

1. Lack of safe contraception for female participants of childbearing potential for the entire study duration
2. Incapacity to give informed consent
3. Not literate in German

### **6.1.6. Exclusion criteria specific to Australia**

1. Incapacity to give informed consent
2. Patient participating in another research protocol including an exclusion period still in progress

## **6.2. Recruitment and informed consent**

Recruitment will target up to 224 participants to allow for drop-outs and to increase the number of participants who will be exposed to the closed-loop system for an enhanced safety and feasibility

assessment. Recruitment will target a minimum quota of 25% of participants using basal insulin and a minimum quota of 60% of participants using multiple daily insulin injections.

Participants will be recruited from outpatient diabetes clinics, primary care centres, social media advertising or other established methods at each of the following sites.

1. Addenbrooke's Hospital, Cambridge University Hospitals NHS Foundation Trust, Cambridge, UK
2. Imperial College Healthcare NHS Trust, London, UK
3. Central Manchester University Hospitals NHS Foundation Trust, Manchester, UK
4. King's College Hospital, King's College NHS Foundation Trust, London, UK
5. Guy's and St Thomas' NHS Foundation Trust, London, UK
6. Norfolk and Norwich University Hospital, Norfolk and Norwich University Hospitals NHS Foundation Trust, UK
7. University Hospitals of Leicester NHS Trust, UK
8. University Hospitals of Derby and Burton NHS Foundation Trust, UK
9. Inselspital, Bern University Hospital, Bern, Switzerland
10. Centre Hospitalier Universitaire (CHU) de Toulouse, France
11. Medical Center – University of Freiburg, Germany
12. Medical University of Graz, Graz, Austria
13. Diabetes Centre, Institute for Clinical and Experimental Medicine, Prague, Czech Republic
14. St Vincent's Hospital Melbourne, Victoria, Australia
15. Forschungsinstitut Diabetes-Akademie Bad Mergentheim (FIDAM GmbH), Bad Mergentheim, Germany

Local GP surgeries in the region of the study site will be included as Participant Identification Centres (PICs) for the UK study sites.

Each centre will aim to recruit between 15-50 participants. Methods of patient recruitment will follow established practices at each centre. Potential participants will be given the study information leaflet and invited to join the study by the research team at least one week before the recruitment visit.

Written informed consent will be obtained from all participants before any study related activities.

## **7. Methods under Investigation**

### **7.1. Name and description of the method of investigation**

The investigational treatment is the CamAPS HX closed-loop app as described in section 3.6 manufactured by CamDiab, Cambridge, UK. The CamAPS HX app is being used in accordance with the instructions for use.

#### **7.1.1 Switzerland requirement only**

The making available on the market, the putting into service or the use of the product to be investigated is not prohibited in Switzerland.

The subjects concerned are not subjected to any additional invasive or stressful procedures compared with those applied under normal condition of use of the product (subcategory A1).

### **7.2. Intended purpose**

The intended purpose of the investigational treatment is automated fully closed-loop insulin delivery. The investigated medical device is used to manage glucose levels in adults with type 2 diabetes, using a fully closed-loop approach.

### **7.3. Method of administration**

The closed-loop system consists of components directly attached to the patient, which are the CGM sensor and the insulin pump. The component not directly attached to the patient is the handheld smartphone that contains the closed-loop algorithm and communicates wirelessly with the insulin pump (Figure 1).

### **7.4. Required training**

Prior to commencement of the study, the research team nurses/clinicians at each of the investigation centres will be trained to use the closed-loop system and its components. Prior to the use of study devices, participants randomised to closed-loop will be trained to use the study CGM device, the study pump and the closed-loop app. Participants randomised to standard insulin therapy will be trained to use the study CGM device. Training will be provided during a 1-2 hour session as an outpatient. Competency assessments of the participants' capability to safely use study devices will be undertaken before the participant is allowed to start using the devices at home.

## **7.5. Precautions**

During treatment with insulin there is a risk of hypoglycaemia and hyperglycaemia. In-hospital testing and hazard analysis have documented reduced risk of hypoglycaemia and hyperglycaemia during closed-loop compared to conventional treatment.

## **7.6. Accountability of the method under investigation**

The local investigators will provide training for the study participants and will make every effort, through regular contact, to ascertain that the closed-loop system is used for the study purposes only. Devices will be identified using serial numbers and the location of investigational devices and their dates of use by participants will be documented throughout the study.

## 8. Study schedule

### 8.1. Overview

The study will be coordinated from the Institute of Metabolic Science, Addenbrookes Hospital, Cambridge, UK and performed at the following sites:

1. Addenbrooke's Hospital, Cambridge University Hospital NHS Foundation Trust, UK
2. Imperial College Healthcare NHS Trust, London, UK
3. Manchester University Hospitals NHS Foundation Trust, UK
4. King's College Hospital, London, UK
5. Guy's and St Thomas' NHS Foundation Trust, London, UK
6. Norfolk and Norwich University Hospitals, UK
7. University Hospitals of Leicester NHS Trust, UK
8. University Hospitals of Derby and Burton NHS Foundation Trust, UK
9. Inselspital, Bern University Hospital, Switzerland
10. Centre Hospitalier Universitaire (CHU) de Toulouse
11. Medical Center – University of Freiburg, Germany
12. Medical University of Graz, Graz, Austria
13. Diabetes Centre, Institute for Clinical and Experimental Medicine, Prague, Czech Republic
14. St Vincent's Hospital Melbourne, Australia
15. Forschungsinstitut Diabetes-Akademie Bad Mergentheim (FIDAM GmbH), Bad Mergentheim, Germany

After recruitment, consent, and a 2-3 week run-in period, participants will be randomised to 26 weeks use of closed-loop insulin delivery or 26 weeks during which they will apply their standard insulin therapy with real-time continuous glucose monitoring.

The study includes up to 5 visits and 6 telephone/email contacts. Visits 2 and 3 may be combined. All participants will continue to be seen by their clinical team at frequencies as appropriate in line with usual clinical practice. All study visits will be scheduled in addition to routine clinical visits and will be performed by the research team. Where possible, for convenience, dates for study visits will be arranged along with routine clinic appointments. Maximum time in the study is 30 weeks. At the end of the study (completion of the final study visit), all participants will return the study devices and resume their pre-study treatment.

**Table 1** outlines study activities when the participant is randomised to closed-loop (intervention group).

**Table 2** outlines study activities when the participant is randomised to standard insulin therapy + CGM (control group).

**Table 1.** Schedule of study visits / contacts when the participant is randomised to closed-loop (intervention group).

|                                           | Visit/
contact | Description                                                                                                                                                                                               | Start relative to previous /
next visit / activity  | Duration   |
|-------------------------------------------|-------------------|-----------------------------------------------------------------------------------------------------------------------------------------------------------------------------------------------------------|--------------------------------------------------------|------------|
| Baseline &
Run-in          | Visit 1    | Recruitment visit: Consent, baseline bloods (inc HbA1c, fasted lipid profile, renal and liver function) height, weight, WHR and BP, urine ACR, urine pregnancy test, questionnaires, masked CGM insertion |                                                        | 1-2 hours  |
|                                           | Visit 2    | Review of baseline bloods and CGM data. Randomisation                                                                                                                                                     | 2-3 weeks after Visit 1 ( $\pm 1$ week);               | 30 minutes |
| Post-randomisation
Training    | Visit 3    | Study pump, CGM and closed-loop training and initiation, competency assessment                                                                                                                            | May coincide with Visit 2, within 2-4 weeks of Visit 1 | 1-2 hours  |
| CL
Intervention
(6 months) | Contact 1         | Review use of study devices; study update                                                                                                                                                                 | within 48 hours after Visit 3                          | 30 minutes |
|                                           | Contact 2         | Review use of study devices; study update                                                                                                                                                                 | 1 week after Visit 3 ( $\pm 3$ days)                   | 30 minutes |
|                                           | Contact 3         | Review use of study devices; study update                                                                                                                                                                 | 1 month after Visit 3 ( $\pm 2$ weeks)                 | 30 minutes |
|                                           | Contact 4         | Review use of study devices; study update                                                                                                                                                                 | 2 months after Visit 3 ( $\pm 2$ weeks)                | 30 minutes |
|                                           | Visit 4    | 3-month visit, HbA1c, fasted lipid profile, renal and liver function, weight, WHR, BP, urine ACR, questionnaires                                                                                          | 3 months after Visit 3 ( $\pm 2$ weeks)                | 1 hour     |
|                                           | Contact 5         | Review use of study devices; study update                                                                                                                                                                 | 4 months after Visit 3 ( $\pm 2$ weeks)                | 30 minutes |
|                                           | Contact 6         | Review use of study devices; study update                                                                                                                                                                 | 5 months after Visit 3 ( $\pm 2$ weeks)                | 30 minutes |
|                                           | Visit 5    | End of closed-loop treatment arm; bloods (HbA1c, fasted lipid profile renal and liver function), weight, WHR, BP, urine ACR, questionnaires +/- interviews; resume usual care                             | 6 months after Visit 3 ( $\pm 2$ weeks)                | 1-2 hours  |

**Table 2.** Schedule of study visits / contacts when the participant is randomised to standard insulin therapy + CGM (control group).

|                                                                | Visit/
contact | Description                                                                                                                                                                                                                     | Start relative to previous /
next Visit / Activity  | Duration   |
|----------------------------------------------------------------|-------------------|---------------------------------------------------------------------------------------------------------------------------------------------------------------------------------------------------------------------------------|--------------------------------------------------------|------------|
| Baseline and
run-in                                 | Visit 1    | Recruitment visit/ screening assessment: Consent, baseline bloods (inc HbA1c, fasted lipid profile, renal and liver function) height, weight, WHR and BP, urine ACR, urine pregnancy test, questionnaires, masked CGM insertion |                                                        | 1-2 hours  |
|                                                                | Visit 2    | Review of baseline bloods and CGM data. Randomisation                                                                                                                                                                           | 2-3 weeks after Visit 1 ( $\pm 1$ week);               | 30 minutes |
| Post-randomisation
training                         | Visit 3    | CGM training and initiation, competency assessment                                                                                                                                                                              | May coincide with Visit 2, within 2-4 weeks of Visit 1 | 1-2 hours  |
| Standard
insulin + CGM
(Control)
(6 months) | Contact 1         | Review use of study devices; study update                                                                                                                                                                                       | within 48 hours after Visit 3                          | 30 minutes |
|                                                                | Contact 2         | Review use of study devices; study update                                                                                                                                                                                       | 1 week after Visit 3 ( $\pm 3$ days)                   | 30 minutes |
|                                                                | Contact 3         | Review use of study devices; study update                                                                                                                                                                                       | 1 month after Visit 3 ( $\pm 2$ weeks)                 | 30 minutes |
|                                                                | Contact 4         | Review use of study devices; study update                                                                                                                                                                                       | 2 months after Visit 3 ( $\pm 2$ weeks)                | 30 minutes |
|                                                                | Visit 4    | 3-month visit, HbA1c, fasted lipid profile, renal and liver function, weight, WHR, BP, urine ACR, questionnaires                                                                                                                | 3 months after Visit 3 ( $\pm 2$ weeks)                | 1 hour     |
|                                                                | Contact 5         | Review use of study devices; study update                                                                                                                                                                                       | 4 months after Visit 3 ( $\pm 2$ weeks)                | 30 minutes |
|                                                                | Contact 6         | Review use of study devices; study update                                                                                                                                                                                       | 5 months after Visit 3 ( $\pm 2$ weeks)                | 30 minutes |
|                                                                | Visit 5    | End of standard insulin + CGM treatment arm; bloods (HbA1c, fasted lipid profile, renal and liver function), weight, WHR, BP, urine ACR, questionnaires; resume usual care                                                      | 6 months after Visit 3 ( $\pm 2$ weeks)                | 1-2 hours  |

## **8.2. Visit 1 - Recruitment visit and screening assessment**

Potential participants will be given a verbal explanation of the study and will have the opportunity to ask any questions. If they agree to proceed with the study, and providing they meet the inclusion/exclusion criteria, participants will give written informed consent to a member of the research team. Those who would prefer to have more time to consider their decision to participate can return and give consent at a later date.

At the screening visit, participant's height, weight, waist hip ratio, blood pressure, demographics, medical and diabetes history, concomitant medications and insulin therapy will be recorded. Participants will have blood tests including HbA1c, fasted lipid profile, renal function and liver function. Urine albumin creatinine ratio (ACR) will be measured. A urine pregnancy test will be performed in all females aged between 18 and 60 years. A masked continuous glucose monitor (CGM) will be applied to assess baseline glycaemic control and participants will be asked to complete questionnaires to assess quality of life and diabetes management.

Participants will then proceed to the run-in period (2-3 weeks) where they will use their usual insulin therapy and wear the masked CGM. For those already using CGM as part of their usual care, they can continue with their usual CGM and also wear the masked study CGM. There will be a minimum of two weeks run-in period for all participants (end of Visit 1 to Visit 2).

## **8.3. Visit 2 - Review of CGM data during run-in period, compliance assessment and randomisation**

At the end of the run-in period (2-3 weeks after Visit 1), participants CGM data will be reviewed. A minimum of 10 days of data recorded will be needed to proceed with randomisation. This visit can be done remotely if preferred.

Eligible participants will be randomised in a 1:1 ratio using a centrally administered web-based randomisation programme to the use of fully closed loop or to standard insulin therapy with CGM for 26 weeks. The randomisation will be stratified by clinical centre and baseline HbA1c.

## **8.4. Visit 3 - Training and initiation of the study devices**

### **8.4.1. Closed-loop (intervention)**

This session will be conducted by a pump educator and/or member of the study team. This visit can be done at the clinical research facility or outpatient department. Study training, where preferred,

can be supported by online training modules and webinars which have been developed for the closed-loop system.

Participants will receive training to cover key aspects of insulin pump use, CGM and closed-loop insulin delivery. Particular attention will be paid to:

- Insulin cartridge and infusion set changes and correct priming procedure
- Insertion and initiation of sensor session
- The impact of diet and lifestyle on glucose sensor readings and trends
- Hypo- and hyperglycaemia management
- Setting and adjustment of alarms/alerts
- Connection and disconnection of the closed-loop system

Written easy to use guidelines for the operation of the insulin pump, CGM and closed-loop system will be provided. Competency in the use of study pump, CGM and closed-loop system will be assessed by the study team. Only participants who demonstrate competency in use of the system will be allowed to continue to the home study phase.

Closed-loop glucose control will start once the training session is completed. Participants will be advised to continue closed-loop over the next 26 weeks. Participants will be asked to contact the study team if they encounter any problems with the closed-loop system.

All non-insulin diabetes therapies will be continued throughout the study period. Throughout the trial, participants and/or the clinical team are free to adjust diabetes therapy as per usual clinical practice.

A subset of participants (n=30, recruited from across UK sites) randomised to the closed-loop group will be invited to take part in a qualitative interview to explore their experiences of using the closed-loop system. These interviews will take place near the end of their participation in the trial.

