#### **8.4.2. Standard insulin therapy with CGM (control)**

This session will be conducted by a pump educator and/or member of the study team. This visit can be done at the clinical research facility or outpatient department. Study training, where preferred, will be supported by online training modules and webinars developed for the CGM system.

Participants will receive training to cover key aspects of the study CGM device. Particular attention will be paid to:

- Insertion and initiation of sensor session

- Interpreting real-time CGM data and trend arrows
- The impact of diet and lifestyle on glucose sensor readings and trends
- Setting and adjustment of alarms/alerts
- Managing hypo- and hyperglycaemia

Written easy to use guidelines for the operation of the CGM device will be provided. Competency on the use of CGM will be assessed by the study team. Only participants who demonstrate competency on use of the CGM will continue to the home study phase.

Standard insulin therapy with CGM will start once the training session is completed. Participants will be advised to use their usual insulin therapy with CGM over the next 26 weeks. Participants will be asked to contact the study team if they encounter any problems with the CGM system.

All non-insulin diabetes therapies will also be continued throughout the study period. Throughout the trial, participants and/or the clinical team are free to adjust diabetes therapy as per usual clinical practice.

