## **8.8. Participant withdrawal criteria**

The following pre-randomisation withdrawal criterion will apply:

1. Participant is unable to demonstrate safe application of insulin therapy as judged by the investigator.

The following pre- and post-randomisation withdrawal criteria will apply:

2. Participant is unable to demonstrate safe use of insulin injections or study insulin pump, CGM and/or closed-loop during post randomisation training period as judged by the investigator.
3. Participants may terminate participation in the study at any time without necessarily giving a reason and without any personal disadvantage
4. Significant protocol violation or non-compliance
5. Recurrent severe hypoglycaemia events related to the use of the closed-loop system
6. Recurrent severe persistent hyperglycaemia events/DKA unrelated to infusion site failure and related to use of the closed-loop system
7. Decision by the investigator or the Sponsor that termination is in the participant's best medical interest
8. Allergic reaction to insulin, or severe reaction to adhesive surface of infusion set or glucose sensor

Participants who are withdrawn for reasons stated in (2) to (8) will be invited to provide a blood sample and complete questionnaires at the end of the planned study intervention.

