### 13.1. Primary Endpoint Analysis

The primary analysis will evaluate the between-group difference in HbA1c at the end of the 26 week intervention period.

The primary analysis will be performed on an intention-to-treat basis using the treatment group assigned by randomisation. Data from participants with or without protocol violation and as appropriate, data from dropouts and withdrawals will be included in the analysis.

Mean  $\pm$  SD or summary statistics appropriate to the distribution will be reported for the primary endpoint by treatment intervention. The treatment interventions will be compared using a linear mixed model with the dependent variable being the primary endpoint and the independent variable being treatment allocation adjusting for baseline HbA1c. A 95% confidence interval will be reported for the difference between the interventions based on the linear mixed model. Residual values will be examined for an approximate normal distribution. If values are highly skewed, then a transformation or robust statistical method will be used instead. However, previous experience suggests that the primary endpoint will follow an approximately normal distribution.

A 5% significance level will be used to declare statistical significance for the primary comparison. A two-sided p-value will be reported. The primary analysis will be a single statistical comparison of a single outcome measure.

A centre-effect will be explored in the analyses by evaluating for interaction between centre and treatment group on the primary outcome. A per-protocol analysis restricted to participants with a minimum of 60% CGM data during control period and 60% use of closed-loop during closed-loop period will be conducted for the primary endpoint.

A detailed analysis plan will be provided separately.

Primary endpoint hypotheses

- Null Hypothesis: There is no difference in the true mean HbA1c at the end of the 26 week period between the two treatment groups.

- Alternative Hypothesis: There is a nonzero difference in the true mean HbA1c at the end of the 26 week period between the two treatment groups.

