### **13.4. Utility Evaluation**

The amount of CGM use will be tabulated for each treatment arm, in addition to the amount of closed-loop system use in the closed-loop arm. Summary statistics appropriate to the distribution and range will be reported.

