### **13.11. Sample size and power calculations**

Data from two completed studies (30, 40) were considered when preparing the power calculations for this study. A sample size of 96 participants (48 per group) was determined to have 90% power to detect a difference in mean HbA1c level between treatment groups, assuming a population difference of 0.8%, an effective SD of the 26 week values of 1.2, and a two-sided type 1 error rate of 0.05. This number was increased to 224 (112 per group) to account for dropouts (assuming a 20% dropout rate) and to increase the number of participants who will be exposed to the closed-loop system for an enhanced safety and feasibility assessment. Recruitment will target a minimum quota of 25% of participants using basal insulin and a minimum quota of 60% of participants using multiple daily insulin injections.

A treatment group difference of  $\geq 0.5\%$  represents a clinically meaningful change in the HbA1c distribution and is generally associated with at least a 50% greater proportion of participants experiencing improvement in HbA1c level by 10% or more, which was shown in the Diabetes Control and Complications Trial to be associated with a substantial risk reduction in diabetic microvascular complications. This is further supported by the results of the United Kingdom Prospective Diabetes Study, which showed that any improvement in HbA1c level is associated with a reduction in risk of diabetic complications.

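### Failing device training after randomisation, or non-compliance, is a reason to leave the study rather than only the device, so the CGM and secondary endpoints can rest on a selected closed-loop group

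*Protocol*

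**What the plan says.** **Order of events.** Under Protocol 8.3, randomisation is at Visit 2. Tables 1 and 2 place device training and the competency assessment at Visit 3, labelled as post-randomisation, although the two visits may be combined. The trial is open-label.

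**What is tested.** Section 8.4.1 tests the closed-loop arm on pump, CGM and closed-loop system, and then states: "Only participants who demonstrate competency in use of the system will be allowed to continue to the home study phase". Section 8.4.2 tests the control arm on the sensor: "Only participants who demonstrate competency on use of the CGM will continue to the home study phase".

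**What follows.** Section 8.8 lists withdrawal criteria that apply before and after randomisation. Item 2 is inability to use the treatment devices safely during post-randomisation training, as judged by the investigator. Item 4 is "Significant protocol violation or non-compliance". Participants withdrawn under items 2 to 8 are invited to give a blood sample and complete questionnaires at the planned end of the intervention. The synopsis adds that efforts will be made to keep participants for the final primary outcome assessment after the intervention is discontinued.

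**What the analysis promises.** Section 13 includes everyone randomised, by intention to treat. Section 13.1 says: "Data from participants with or without protocol violation and as appropriate, data from dropouts and withdrawals will be included in the analysis". Section 15 speaks of using data obtained before withdrawal. Section 13.2 tests four key endpoints in fixed sequence after the primary, all from CGM over 26 weeks. Section 13.4 tabulates "the amount of closed-loop system use in the closed-loop arm" without a denominator.

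**The concern.** Competency and compliance are observed after allocation, and what has to be mastered depends on the arm. Current pump and closed-loop users are excluded (6.1.2), so the pump is not part of anyone's current treatment at entry. The sensor has already been worn, masked, for at least 10 days before randomisation (8.3). More failures in the closed-loop arm are therefore plausible, and people who struggle with the system may well have worse glucose control than those who master it.

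If such participants left only the device, the intention-to-treat comparison would be intact. The protocol has them leave the study. Someone removed at Visit 3 has baseline data but no post-randomisation CGM, no 3-month visit, and no later weight, blood pressure or ACR. The closed-loop results on those endpoints would then describe people who could and did use the system, not everyone offered it. An analysis plan written later can choose a missing-data method, but it cannot recover measurements that were never taken.

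**Working it through.** **1. The plan's own sample size.** Inputs from 13.11: "A sample size of 96 participants (48 per group) was determined to have 90% power", "assuming a population difference of 0.8%, an effective SD of the 26 week values of 1.2", and "a two-sided type 1 error rate of 0.05".

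n per group = 2 × (1.960 + 1.282)² × 1.2² / 0.8² = 2 × 10.51 × 2.25 = 47.3, rounded up to 48, so 96 in total. The stated figure reproduces.

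**2. Is loss of numbers the problem?** No. With 112 per group, power for a 0.8% difference is 99.9%. After 20% loss in each arm it is 99.4%. With 30% loss in closed-loop and 20% in control it is 99.1%. The issue is who is lost.

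**3. What is collected after withdrawal under 8.8(2) or (4).**

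| Measure | Planned after withdrawal? |
|---|---|
| Week-26 HbA1c (primary) | Yes, by invitation (8.8), plus the synopsis retention effort |
| Questionnaires | Yes, by invitation, at the planned end |
| CGM over 26 weeks (four key endpoints) | Not stated |
| 3-month visit | Not stated |
| Weight, blood pressure, urine ACR | Not stated |

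**4. Size if removed participants are unmeasured.** Let f be the fraction of the closed-loop arm removed and unmeasured, and D the amount by which their HbA1c exceeds that of those retained. The full-arm mean is the retained mean plus f × D, so the analysis of retained participants flatters closed-loop by f × D. Because the model adjusts for baseline HbA1c, D is the gap left after that adjustment.

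Both inputs are assumptions:
- f = 3% to 10%, which is 0.03 × 112 ≈ 3 to 0.10 × 112 ≈ 11 participants. The protocol gives no failure rate.
- D = 0.5 to 1.4 points. The upper value borrows the contrast of 57 against 72 mmol/mol in 3.4.3. The protocol equates 7% with 53 and 15% with 140 mmol/mol, so one mmol/mol is 8/87 = 0.092 points, and 15 × 0.092 ≈ 1.4. This is a treatment contrast from a crossover study, not an observed gap between removed and retained participants.

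Low end: 0.03 × 0.5 = 0.015 points. High end: 0.10 × 1.4 = 0.14 points. The high end is 0.14/0.5 = 28% of the difference that 13.11 calls clinically meaningful, and 0.14/0.8 = 17.5% of the assumed effect.

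If the week-26 sample is obtained from those removed, f is zero for HbA1c and so is the bias.

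**5. The same arithmetic for time in range.** Here the blood sample does not help. If removed participants fell short by the full 35 percentage points between treatments in 3.4.3 (again a borrowed figure), the overstatement is 0.03 × 35 = 1.1 to 0.10 × 35 = 3.5 percentage points.

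**6. Reported closed-loop use.** Assume 90% use among those retained and zero among those removed. Over all randomised, use is 0.97 × 90 = 87.3% at f = 3% and 0.90 × 90 = 81.0% at f = 10%. Leaving removed participants out gives 90%.

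**The case against.** A reader might go further and infer that the arms stop being comparable and that device use is measured only in those who comply. The documents do not support either statement.

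- **Primary endpoint.** The analysis covers all randomised participants, those withdrawn under 8.8(2) to (8) are invited to give the end-of-study sample, and the synopsis promises retention efforts. This stands. What remains is that an invitation is not a scheduled visit.
- **Device use.** Section 13.4 does not restrict the tabulation to compliers. Someone who never starts has a known use of zero, so the denominator is a reporting choice that a separate analysis plan could settle. The inflation is possible, not planned.
- **Low users.** Item 4 of 8.8 is not defined as low closed-loop use. The per-protocol set in 13.1, which requires 60% use, implies that lower users remain in the main analysis. It cannot be said that item 4 removes low users as a class.
- **Unequal hurdle.** The checks differ in scope, three components against one, but no failure rate is given and the synopsis allows further training. Item 2 of 8.8 also covers insulin injections, so it can apply to controls. How much harder the closed-loop check is cannot be judged from the text.
- **Magnitude.** The figures rest on assumed inputs, assume no measurement of those removed, and take control as fully observed. At the low end the effect is negligible.
- **No contradiction.** Withdrawal criteria and intention to treat often coexist. That is true, but here the withdrawal rule ends collection of data that the stated analysis population needs.

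**Conclusion.** The point holds in limited form. Competency is judged after randomisation on different content in each arm, and failing it or being non-compliant is a criterion for leaving the study. For HbA1c the risk is modest: zero if the invited sample is obtained, and about 0.015 to 0.14 points in favour of closed-loop if 3-10% are removed unmeasured with HbA1c 0.5-1.4 points worse. For the four key CGM endpoints, and for weight, blood pressure and ACR, no collection is planned after withdrawal. Those results can therefore rest on a selected closed-loop group, against the commitment in Section 13 to analyse everyone randomised. The actual size depends on how many participants are removed, which the protocol does not say. The change is worth making because it is cheap and can only be made while data are still being collected.

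**What to change.** - **Sections 8.8(2) and (4), with matching text in the synopsis, 8.4.1 and 8.4.2:** distinguish not starting or stopping the study device from leaving the study. State that participants in the first situation stay in their assigned group for all remaining visits, for HbA1c and, where feasible, for CGM collection.
- **Reconcile four places:** the synopsis retention statement, the invitation in 8.8, the qualified inclusion of dropout data in 13.1, and the reference in Section 15 to data obtained before withdrawal.
- **Section 13.4:** report closed-loop use over all participants randomised to that arm, counting zero when the device is not used.

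The competency check itself, and the treatment of anyone who does not pass it, remain with the clinical team; nothing here asks for a change to either. The cost is protocol wording, a few extra visits for participants who would otherwise leave, and possibly a lower reported usage figure.
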